## Abstract

**Background:**

Low levels of physical activity, musculoskeletal morbidity and weight gain are commonly reported problems in children with cancer. Intensive medical treatment and a decline in physical activity may also result in reduced motor performance. Therefore, simple and inexpensive ways to promote physical activity and exercise are becoming an increasingly important part of children’s cancer treatment.

**Methods:**

The aim of this study is to evaluate the effect of active video games in promotion of physical activity in children with cancer. The research is conducted as a parallel randomized clinical trial with follow-up. Patients between 3 and 16 years old, diagnosed with cancer and treated with vincristine in two specialized medical centers are asked to participate. Based on statistical estimates, the target enrollment is 40 patients. The intervention includes playing elective active video games and, in addition, education and consultations for the family. The control group will receive a general recommendation for physical activity for 30 minutes per day. The main outcomes are the amount of physical activity and sedentary behavior. Other outcomes include motor performance, fatigue and metabolic risk factors. The outcomes are examined with questionnaires, diaries, physical examinations and blood tests at baseline and at 2, 6, 12 and 30 months after the baseline. Additionally, the children’s perceptions of the most enjoyable activation methods are explored through an interview at 2 months.

**Discussion:**

This trial will help to answer the question of whether playing active video games is beneficial for children with cancer. It will also provide further reasoning for physical activity promotion and training of motor skills during treatment.

**Trial registration:**

ClinicalTrials.gov identifier: NCT01748058 (October 15, 2012).

## Background

The risk of any child developing pediatric cancer is 1–2/10,000, and about one-third of these cases are leukemias [1]. Because of the improvements in treatments, the overall survival rate has increased, and 5 years after diagnosis over 80% of the diseased children are still alive.

Previous studies indicate that children with cancer gain weight during their treatment and have difficulties in returning to their normal weight after treatment [2]. Younger patients in particular start to gain weight as early as 6–12 months after diagnosis and usually continue to gain weight for one year after their treatment [3-6]. Low physical activity and being overweight may lead to an increased risk of chronic diseases, such as metabolic syndrome, type two diabetes and cardiovascular diseases [7]. Children with cancer are also at increased risk of osteoporosis [8]. Furthermore, long-term survivors of childhood cancer, especially leukemia, have been reported to have problems with bone mineral density [9] and lower fitness than age mates [10]. Good physical fitness is probably the most important factor in achieving a normal bone mass in childhood leukemia survivors [11].

Cancer treatments such as vinca-alkaloids may cause peripheral motor or sensory neuropathy, leading to clumsiness, muscular weakness and deficient motor skills. Children with cancer may also suffer from reduced muscle elasticity and ligament laxity [12-15]. Peripheral neuropathy, muscle weakness and mobility deficits may also continue years after treatment [16,17]. Normal participation in physical activity, school physical education classes and group activities are interrupted at a time when the child’s motor skill development is rapid and highly important [18]. The child’s protected condition and an increased risk of infection result in a secluded life. Thus, when physical activity decreases, due to many factors during treatment [19], and the disease and the treatment’s side effects affect the child, his/her motor performance and motor skill development usually lags behind that of healthy peers. Furthermore, physical fitness is lower in acute lymphoblastic leukemia (ALL) survivors than in their healthy peers [20].

Most studies reporting physical activity levels in children with cancer have investigated the phenomenon in the maintenance phase or years after treatment; only a few studies have focused on physical activity levels during early treatment [21,22]. It is known that during the first year of treatment children with cancer perform significantly less moderate-to-vigorous physical activity than healthy controls, indicating that these children remain mostly inactive during the initial year of treatment even though the recommendations encourage age-appropriate physical activity that is also individually appropriate [23]. Physical activity recommendations for children with ALL indicate that at the maintenance phase of treatment they should progress to an activity level close to the recommendations set for healthy children [24]. During the induction and consolidation phase, light physical activity according to the individual’s condition is recommended. [24]. In a recent randomized trial [25] in which the recruitment was conducted at the time of diagnosis and the intervention group received exercise program at the beginning of the cancer treatment motor performance and passive ankle dorsiflexion decreased equally in both groups. Also the body fat increased similarly in both groups. Hartman et al. [25] suggest that this was due to unsatisfactory commitment to the exercise program. Therefore it is important to develop motivating exercise programs.

Physical activity and different exercise programs during cancer therapy have been approved as beneficial in improving children’s cardiovascular fitness, muscle strength, motor performance and flexibility and in reducing fatigue [26]. Physical activity and exercise interventions have been found to be particularly effective when carried out in supervised settings like in hospital environment [19,27,28]. However, the evidence is still limited due to small sample sizes and lack of randomization in most trials. Therefore, it is necessary to develop and produce evidence of safe, effective exercise and motivating interventions for children with cancer.

Active video games, such as Nintendo Wii™ (Nintendo Co., Ltd., Kyoto, Japan) Xbox Kinect (Microsoft Co., Redmond, WA, USA) and Konami Dance Dance Revolution (Harmonix Music Systems Inc., Cambridge, Massachusetts, USA), have become amazingly popular among children and adolescents. For instance, the market best seller, Nintendo Wii™, sold 99 million games consoles in 2012 worldwide [29]. An active video game is one in which playing the game is based on the player’s movements. Thus, these games may provide one possibility for decreasing sedentary screen time and motivating children to be more physically active. The explosive popularity of these games has also inspired physiotherapists and other health professionals to use and study them in rehabilitation [30-32]. Even though these games may not be the solution to achieving the recommended physical activity in healthy children, they might be helpful in breaking up sedentary time in some special circumstances, such as during hospitalization or isolation. These games are also feasible for cancer patients because they can be played in patient rooms, where the risk of infection is minimized. In addition, children are motivated to play them, as they are safe and fun to play [33].

Evidence for and against active video gaming to promote physical activity exists, but most studies concerning active video games used for rehabilitative purposes have produced positive results [30]. Playing active video games in laboratory circumstances raises healthy children’s energy consumption and heart rate. Active video-game play equals light-to-moderate physical activity [31,32], but in more naturalistic settings, like at home, the results have not been as promising [34]. Baranowski et al. [34] suggest this to be due to unsupervised settings where players did not reach the needed intensity or compensated the increased physical activity by being less active at other times of the day [34]. However, in rehabilitation and restricted circumstances, such as during hospital stays, these games may have benefits. In healthy population, active video games may not be an alternative to being physically active but can be useful in populations with limitations, as these games can be played even when being seated. A review by Primack et al. showed that active interventions based on video games improved 59% of the physical therapy outcomes, 50% of the physical activity outcomes and 42% of pain distraction outcomes [30]. Nevertheless it should be noticed that the quality of the studies concerning active video games has mostly been poor [30].

Active video games have been studied also in children with cerebral palsy [35,36], developmental delay [37] or disability [38], acquired brain injury [39] and lower limb amputations [40] with promising results [30] but, to the best of our knowledge, active video games have not yet been studied in children with cancer alone. However, there is a protocol published in which active video gaming is used for exercise purposes in pediatric autologous stem cell transplant patients [41].

### Study aims

The primary aim of this study is to evaluate the efficacy of active video games with regard to the promotion of physical activity in children with cancer. The ultimate goal is to motivate children with cancer and their families to integrate active lifestyle choices into their everyday life, even during treatment, to decrease the negative impact of high levels of sedentary behavior. The results will help answer the question of whether playing active video games has a positive effect on the health of children with cancer.

Our hypothesis is that the possibility to play active video games and guidance given to the family about physical activity during cancer treatment promote children’s physical activity and shorten sedentary periods when compared to the control group, who receive only a general recommendation to be active.

The detailed research questions and hypotheses of the study are:

1. Is playing active video games effective in increasing the physical activity of children with cancer during cancer treatment?

a) It is hypothesized that the possibility of playing active video games during cancer treatment promotes children’s physical activity compared to controls.

2. Is playing active video games effective in promoting motor performance during cancer treatment?

b) It is hypothesized that children’s motor performance in the intervention group is maintained better than in the control group.

3. Is playing active video games effective in reducing experienced fatigue by children with cancer?

c) It is hypothesized that the children in the intervention group experience less fatigue during cancer treatment than the children in the control group.

4. Do playing active video games have impact on children’s body mass index and the development of metabolic risk factors in children with cancer?

d) It is hypothesized that playing active video games has a positive impact on children’s body mass index and metabolic risk factors during cancer treatment.

5. What are the children’s and families’ perceptions of the most enjoyed activation methods during cancer treatment?

The protocol follows the methodological guidelines for clinical trials outlined in the CONSORT statement [42].

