### Intervention

The physical activity in the intervention is based on active video gaming. The intervention consists of playing elective active Nintendo Wii™ games daily, for at least 30 minutes, during hospitalization and at home for 8 weeks in total, with consideration of the participants’ individual conditions. Physical activity is not allowed during fever and vomiting or nausea episodes, or if the medical condition changes acutely. The physical activity intensity is recommended as light-to-moderate. One way to monitor the relative intensity of activity is to monitor the respiration and breathing rate during the activity [45]. The parents are guided that light-to-moderate intensity physical activity equals only to slightly increased breathing rate, still feeling “easy to breath” or “slight breathlessness” and they are advised to monitor the child’s condition before and during the physical activities. At the beginning of the study, the attending physician verifies the children’s ability to physical activity, and, if there are significant changes to the child’s condition, the researcher and the physical therapists who conduct the motor performance testing are informed. The children receiving anthracycline therapy are also followed by a cardiologist and regular echocardiograms.

The intervention includes information and recommendations for physical activity and guidance on which Nintendo Wii™ Fit games to play and how to play them. All children in the intervention group will receive the same written instructions and individual face-to-face teaching, where examples about suitable games for each age group are presented. For 3- to 6-year-old children, games such as Hola hoop or Jogging are recommended based on the easiest difficulty levels. For children aged 7- to 10-years, the recommended games include such as Island Cycling, Rhythm Kung-Fu, Hola hoop and Jogging and for 11- to 16-year-old children there are recommended games from all the four types of exercises (aerobics, balance, strength training, yoga). This guidance and instruction are given by a physiotherapist in the hospital. The physiotherapist contacts the participants in the intervention group via telephone for consultation during the intervention in order to encourage children to play and be active. Children in the intervention group have the game console and games at home for the duration of the intervention period.

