Some limitations of the intervention must be mentioned: children may learn to play the games with incorrect execution of movements, which decreases the amount of activity while playing. However, the physical therapist teaches the games to the intervention group as they should be played, and parents are guided to watch that the children play them correctly. It is also more difficult to cheat the balance board used in the intervention than the remote control, and even if the child is executing a movement incorrectly, playing the game still needs advanced coordination with the timing of the movements. The second concern about the intervention is that how well the smallest enrolled children can experience success when playing the game. Too difficult tasks may promote boredom and unsatisfactory commitment to the program. This might be the case among the very youngest children enrolled to the study. However, our experiences have been positive so far. After this study we get valuable directions to develop the intervention further and even new easier activity promoting video games might have come to the market.

If the children or guardians have questions about the intervention or physical activity recommendations they are guided to contact the ward or the research group. If the question is about the child’s health, they are guided to contact the ward staff. Both study wards and their staff are well informed about the ongoing study and will let the researcher know of any questions concerning the study or its procedures.

In this study, the control group receives only general advice for physical activity for 30 minutes per day. They do not receive guidance on playing active video games or telephone consultations after being discharged from the first medical treatment period. The controls have the normal treatment so that if they need physical therapy referral or consultation from a physical therapist they will receive the normal treatment similarly as the children in the intervention group. All the physical therapy session documentation is collected in the end of the study and will be taken into consideration when analyzing and reporting the data.

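### The aim, research questions 1–4, hypotheses a and d and the planned conclusions credit the games alone, but the randomised comparison tests games plus guidance and telephone support against general advice

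*Protocol article*

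**What the plan says.** Under Study aims, the protocol article states: "The primary aim of this study is to evaluate the efficacy of active video games with regard to the promotion of physical activity". The first research question is "Is playing active video games effective in increasing the physical activity of children with cancer during cancer treatment". Questions 2 to 4 put the same cause, playing the games, before motor performance, fatigue, and body mass index with metabolic risk factors. Hypotheses a and d also name only the games or the chance to play them. The abstract's Discussion carries this into the expected conclusion: "This trial will help to answer the question of whether playing active video games is beneficial for children with cancer". The main Discussion section does likewise.

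Other parts describe something wider. The overall hypothesis, also under Study aims, credits "the possibility to play active video games and guidance given to the family about physical activity during cancer treatment" and sets this against a control group given only a general recommendation. The abstract's Methods paragraph says: "The intervention includes playing elective active video games and, in addition, education and consultations for the family". The Intervention section begins its list of contents with "The intervention includes information and recommendations for physical activity and guidance on which" Wii Fit games to play. It adds written instructions and individual teaching, and says that a physiotherapist "contacts the participants in the intervention group via telephone for consultation during the intervention in order to encourage children to play and be active".

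Controls get general advice to be active for 30 minutes per day. Of them the Intervention section says: "They do not receive guidance on playing active video games or telephone consultations after being discharged from the first medical treatment period". Ordinary physical therapy, when needed, is available to both arms.

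**The concern.** The article states its purpose in two ways that do not mean the same thing. One is an effect of playing active video games. The other is an effect of games together with guidance for the family. A two-arm trial of the package against general advice tests only the second.

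What is at stake is the claim made from a positive result. If it is reported in the words of the aim and questions 1–4, readers will take it as evidence that the games raise activity. A ward that supplied consoles without the guidance and the calls would then be relying on an effect the trial had not estimated. The limitations given in the Intervention and Discussion sections cover incorrect play, difficulty for the youngest children, the Hawthorne effect, the accelerometer and dropout. None says that the games cannot be separated from the support that comes with them.

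**Working it through.** **1. What differs between the arms** (abstract Methods; Intervention)

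- Console and games at home: intervention arm only.
- Teaching on which games to play and how: intervention arm only. This is largely the means of delivering the games, so it is not counted below as a rival ingredient.
- General activity information and recommendations, with family education and consultations: intervention arm. Controls get the 30-minute general advice.
- Telephone encouragement: intervention arm only. Its stated purpose covers being active as well as playing.
- Ordinary physical therapy when needed: both arms, with session records collected.

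So the games differ between arms, and so do at least two separable kinds of support: general guidance and education, and telephone encouragement.

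**2. Which statements match that contrast** (Study aims; abstract; Discussion)

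- Games alone: primary aim, questions 1–4, hypotheses a and d, and the conclusions in the abstract and the main Discussion.
- Package against control: the overall hypothesis.
- Arm against arm, with no cause named: hypotheses b and c. These fit the design as they stand.

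**3. What the design identifies**

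Write the expected difference between arms as

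Δ = G + S + I,

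where G is the effect of the games, S that of guidance, education and calls, and I any interaction. The Trial design section gives two arms, and neither receives S without G. The data therefore estimate Δ only: one equation, three unknowns. A difference of 360 cycles per day fits G = 360 with S = I = 0. It fits G = 180 and S = 180 with I = 0 equally well, and G = 0 and S = 360 with I = 0. These splits are illustrations; the documents give no split.

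**4. What the sample size refers to**

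Inputs from Sample size calculation: difference in change 360, SD of change 360, 5% significance level, 80% power. Sidedness is not stated; two-sided is assumed.

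- Standardised difference = 360 / 360 = 1.0.
- Normal approximation: n per arm = 2 × (1.960 + 0.842)² / 1.0² = 15.7, so 16 per arm and 32 in total.
- Two-sample t-test: 16.71, so 17 per arm and 34 in total, which is the article's figure. Power at 17 per arm is 0.807.

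The figure reproduces. The 360 is defined as the difference between groups, so it is Δ, the package contrast, and not G.

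**The case against.** The strongest reply is that nothing is hidden. The abstract lists education and consultations as additional to the games, the overall hypothesis names the package, and the Intervention section itemises what each arm gets. Naming a programme after its main component is common shorthand, and the concluding sentences are cautious statements of purpose. All of this is fair, and it is why the matter is one of wording. It does not remove the conflict within Study aims: the aim and questions are what a results paper answers, and they are put more narrowly than the comparison.

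Two further points are right and limit the criticism. The face-to-face teaching mainly shows children how to play and belongs to delivering the games. Both arms can also have physical therapy when needed, so controls are not without professional contact.

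A reader might go further and infer that the extra contact is the true active ingredient. The documents do not show that. The Background says exercise interventions work particularly well in supervised settings such as hospital, but a telephone call that encourages play at home is not supervision. The text makes an effect of contact plausible and no more.

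A reader might also hope that the activity diary could settle the question, since it records game play as its own category. It cannot. The Background allows that games may motivate children to be more active generally, so a gain outside game play could come from the games. It also describes compensation by lower activity at other times, which could hide an effect of guidance. The calls promote play too, so their effect could appear as game time. The article itself says that the diary data may be imprecise.

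**Conclusion.** The point holds as a mismatch between the stated claim and the comparison made. The primary aim, questions 1–4, hypotheses a and d and the planned conclusions attribute to the games an effect that the trial estimates only for the games with general guidance, family education and telephone encouragement. It should be corrected, because it decides what a positive result may be said to show.

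It would be wrong to infer that the randomised comparison is biased or invalid: it is sound for the package, and the planned size reproduces for that contrast. Nor are all four lettered hypotheses at fault, since b and c already compare the arms.

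No number can be put on the games' share. To say that it lies anywhere from none to all would mean only that it is not identified. Even those limits assume that no component works against another, and the compensation described in the Background makes that uncertain.

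The conclusion rests on one judgement: that general activity guidance, family education and calls to be active are separable from playing the games. The abstract's own wording, which presents education and consultations as additional, supports it.

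**What to change.** - Reword the primary aim, research questions 1–4, hypotheses a and d, and the planned conclusions in the abstract and Discussion, in line with the overall hypothesis. For example: the effect of an active video game programme with family guidance and telephone support, compared with general advice to be physically active. Leave hypotheses b and c as they are.
- Add one sentence to the limitations saying that the games' separate contribution cannot be estimated, because no group receives the guidance and telephone support without the games.
- If wanted, report diary time outside game play by arm as a descriptive table, with a note that it does not separate the effect of guidance from that of the games.

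No change to arms, sample size, outcomes or data collection is needed. The cost is some redrafting and, if chosen, one table from data already collected. The downside is a narrower claim about the games.
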